### Strategies to improve adherence to interventions {11c}

Adherence to treatment schedules will be assessed by pill counts at study visits by direct questioning of dosing schedules and missed doses, telephone visits, and self-report. Participants shall be followed-up in clinic regularly to receive timely and comprehensive consultation and monitoring in the process of treatment. They are in close contact with the investigators in different centers and monitor progression during study visits. This study will use the Chinese Rheumatism Data Center (CRDC) platform [22] and the application of CRDC to ensure regular and standardized follow-up of every patient.

### Relevant concomitant care permitted or prohibited during the trial {11d}

Except for medication which may be required to treat adverse events, no medication other than study drugs will be allowed from the first dosing until all the end of study evaluations have been conducted.

Participants were allowed to use glucocorticoids but the dosage should be less than or equal to 10 mg prednisone per day. Other immunosuppressants including methotrexate, azathioprine, mycophenolate mofetil, cyclosporine, and tacrolimus were not permitted during the whole study. Plasma exchange and IVIg were prohibited during the study. Drugs that promote salivary secretion, such as anethole trithione and pilocarpine, sodium hyaluronate eye drops, and artificial tears shall not be used within 7 days before randomization and evaluation of exocrine gland function.

### Provisions for post-trial care {30}

The project will provide insurance to all participants for damage caused by the therapies of the study. All participants with post-recruitment illness will be monitored until symptoms resolve, until laboratory changes return to baseline, or until there is a satisfactory explanation for the changes observed. They will receive essential medical care at different centers described above.

### Outcomes {12}

#### Primary outcome measure

The rate of ESSDAI response, or MCII of ESSDAI, which was defined as an improvement of ESSDAI at least three points, at 12 weeks.

#### Secondary outcome measure

Rate of MCII of ESSDAI at 24 weeks.Rate of EULAR pSS patient-reported index (ESSPRI) response, or MCII of ESSPRI, which was defined as an improvement of ESSPRI at least one point or 15%, at 12 and 24 weeks.Change of Physician’s Global Assessment (PGA) score from baseline at 12 and 24 weeks.Change of serological activity parameters including CRP, ESR, IgG, and RF levels from baseline at 12 and 12 weeks.Change of salivary glands function including the salivary flow rate (ml/min) and the Schirmer’s test (mm) from baseline at 12 and 24 weeks.Change of focus score on labial salivary gland biopsy [23] from baseline at 24 weeks. The minimum value is 1 and maximum value is 12, and higher scores mean a worse outcome.

### Participant timeline {13}

Table 2 shows the participant timeline. The window period of each visit is 2 weeks.

**Table 2 Tab2:** The participant timeline

	− 4 weeks (screening)	0 weeks (start medication)	4 weeks	8 weeks	12 weeks (switch checkpoint)	16 weeks	20 weeks	24 weeks (the end of study)
Visit	0	1	2	3	4	5	6	7
informed consent	√							
Medical history record	√							
Vital signs	√	√	√	√	√	√	√	√
Infection screening like hepatitis and TB	√							√
complete blood cell count	√	√	√	√	√	√	√	√
Renal and liver function test	√	√	√	√	√	√	√	√
Urine routine test	√	√	√	√	√	√	√	√
Acute phase reactants (ESR, CRP)	√	√			√			√
Autoantibodies (antinuclear antibody, anti-SSA, anti-SSB, et al.)	√							√
Immunological parameters (Ig, complement, RF)	√				√			√
Exocrine gland function	√				√			√
Labial salivary gland biopsy	√							√
PGA score	√	√			√			√
ESSDAI score	√	√			√			√
ESSPRI score	√	√			√			√
Adverse events	√	√	√	√	√	√	√	√
Concomitant medication	√	√	√	√	√	√	√	√

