### Trial design {8}

This is a multi-center, prospective, open-label, randomized study to compare the efficacy of baricitinib + hydroxychloroquine (HCQ) with HCQ alone in pSS patients. Patients will be randomized (2:1) to receive baricitinib 4 mg per day + HCQ 400 mg per day or HCQ 400 mg per day alone. We will switch HCQ to baricitinib + HCQ if the patient in the latter group has no response at week 12. The final evaluation will be at week 24.

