### Eligibility criteria {10}

#### Inclusion criteria

Must read and understand the informed consent approved by the institutional review board (IRB)/ethics review board (ERB) governing the site and provide written informed consent.Stated willingness to comply with all study procedures and availability for the duration of the study.Ability to take oral medication and be willing to adhere to the study intervention regimen.Male or female, aged between 18 and 75 years.Fulfill the 2016 ACR/EULAR classification criteria for pSS [19].With moderate activity (ESSDAI ≥ 5) on HCQ 400 mg per day treatment for at least 12 weeks at the screening visit.With serological activity defined as hypocompleminemia or elevated C-reactive protein (CRP)/erythrocyte sedimentation rate (ESR)/immunoglobulin G (IgG) /rheumatoid factor (RF) level (excluding acute and chronic infection and other factors).Nonpregnant, nonbreastfeeding female patient.Males with potential for reproduction must agree to practice effective birth control methods described above too.

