## Statistical methods

### Statistical methods for primary and secondary outcomes {20a}

Data will be analyzed using IBM SPSS 23.0 (Chicago, IL, USA). Differences will be considered statistically significant if *p* < 0.05. Continuous variables were analyzed using paired *t*-tests for data comparison between the two treatment groups. Categorical variables were analyzed using the chi-square test or Fisher’s exact test, where appropriate. Two-tailed tests were used for all analyses, and *P* < 0.05 was considered statistically significant. The 95% confidence interval of the fixed effect size will be used to assess whether treatment difference reaches the minimally clinical important difference. The changes in outcome measures among all participants at 24 weeks will be used for intention-to-treat analyses.

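### IgG and RF have no week-0 draw, so their only scheduled pre-dose value is about 4 weeks old and may be the one that qualified the patient; the time points of this outcome are also misprinted

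*Protocol article*

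**What the plan says.** **Schedule (Participant timeline {13}, Table 2).** Treatment begins in the column headed "0 weeks (start medication". The two serology rows are ticked differently:

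| Row | Screening (week -4) | Week 0 | Week 12 | Week 24 |
|---|---|---|---|---|
| "Acute phase reactants (ESR, CRP" | yes | yes | yes | yes |
| "Immunological parameters (Ig, complement, RF" | yes | no | yes | yes |

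Blood count and renal and liver tests are also ticked at week 0, as are ESSDAI, ESSPRI and PGA.

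**Entry (Inclusion criteria).** One criterion reads: "With serological activity defined as hypocompleminemia or elevated C-reactive protein (CRP)/erythrocyte sedimentation rate (ESR)/immunoglobulin G (IgG) /rheumatoid factor (RF) level". Any one of the five is enough.

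**Outcome (Secondary outcome measure).** The serological outcome is: "Change of serological activity parameters including CRP, ESR, IgG, and RF levels from baseline at 12 and 12 weeks". The article does not say which visit is baseline.

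**Analysis (Statistical methods {20a}).** "Continuous variables were analyzed using paired *t*-tests for data comparison between the two treatment groups".

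**The concern.** For IgG and RF the screening draw is the only scheduled measurement before treatment. Two things follow for change within an arm.

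- The interval is longer than the label suggests, because it includes the weeks between screening and first dose.
- A patient admitted because IgG or RF was raised has that same raised value as the starting point. A value picked for being high tends to be lower on repeat even if nothing is done, so part of such a patient's later fall may be regression to the mean.

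This would matter little if change were only compared between arms. But the method named for continuous variables is a paired t-test. Two independent randomised groups cannot be paired; applied as named, the test becomes a before-after test within an arm, which cannot tell regression to the mean from a drug effect. At stake is the reading of one secondary outcome.

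The stated time points raise a separate, simple problem: week 12 appears twice and week 24 not at all.

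**Working it through.** The plan gives no figure on this point, so there is none to reproduce.

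**1. Interval.** Screening is at week -4. Change to week 12 spans 12 - (-4) = 16 weeks, and change to week 24 spans 24 - (-4) = 28 weeks. Both are approximate, since each visit has a 2-week window.

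**2. Patients selected on the marker itself.** Assumptions, not in the documents: the marker is roughly normal in SD units, patients are taken above a cut-off c, and screening and follow-up values correlate at r. With no treatment effect,

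expected fall = (1 - r) × φ(c) / (1 - Φ(c)).

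For c = 0.5 the ratio is 0.3521 / 0.3085 = 1.141. The fall is then:
- r = 0.9: 0.1 × 1.141 = 0.11 SD
- r = 0.8: 0.2 × 1.141 = 0.23 SD
- r = 0.7: 0.3 × 1.141 = 0.34 SD

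**3. The protocol's own rule, any of five markers.** Simulation with no treatment effect: each visit's value is √r × true level + √(1 - r) × noise; true levels of the five markers correlate at 0.3 (assumed); a patient enters if any marker passes the cut-off at screening. Mean change in one marker, screening value as baseline, in SD:

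| r | Cut-off (SD) | Entry on this marker only | Entry on any of five |
|---|---|---|---|
| 0.6 | 0 | -0.319 | -0.017 |
| 0.6 | 1 | -0.606 | -0.084 |
| 0.8 | 0 | -0.158 | -0.010 |
| 0.8 | 1 | -0.304 | -0.044 |
| 0.9 | 0 | -0.078 | -0.004 |
| 0.9 | 1 | -0.154 | -0.021 |
| 0.95 | 0 | -0.039 | -0.003 |
| 0.95 | 1 | -0.077 | -0.011 |

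The average over the OR rule is thus about 0.003 to 0.08 SD, larger at the stricter cut-off.

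**4. Chance that a before-after paired test calls this a fall.** Approximation: Φ(|d|√58 - 1.96), where d is the mean change divided by its SD and 58 is the planned size of the baricitinib arm. With no shift it returns 0.025. If all 58 had entered on the marker, it gives 0.15 to nearly 1.00. Under the OR rule it gives about 0.03 to 0.10.

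**5. Between arms.** Both arms pass the same entry rule. The simulated difference in mean change stays within about 0.01 SD of zero throughout.

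**6. With a separate week-0 value as baseline.** Assuming equal correlation between all visits, mean change is -0.002 to +0.007 SD, in effect zero.

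**7. Time points.** Table 2 collects all four named markers at weeks 12 and 24. The outcome text names week 12 twice.

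**The case against.** The strongest reply is that the trial is randomised with a concurrent control: "Patients will be randomized (2:1) to receive baricitinib 4 mg per day + HCQ 400 mg per day or HCQ 400 mg per day alone". Both arms are selected alike, so regression to the mean cancels in expectation. This stands in full. A reader might infer a biased treatment effect, and the documents do not support that.

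Second, the entry rule is an OR over five markers. A given IgG or RF value need not have qualified the patient, so the larger figures describe a subgroup whose share the documents do not give. This also stands, and it makes the OR-rule average the fairer summary for a whole arm.

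Other readings go further than the text allows:

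- *That the outcome mixes two baselines.* ESR and CRP also have a screening value, so one common screening baseline is possible. A mixture would arise only if the analysis chose week 0 for some markers, and the article does not say so.
- *That the primary endpoint is affected.* ESSDAI is itself scheduled at week 0, and the article does not print the components of the score.
- *That markers are still drifting after immunosuppressant withdrawal.* Listed agents are excluded within 4 weeks of screening, about 4 + 4 = 8 weeks before first dose. No figure for residual drift is given, and any drift would act on both arms.
- *That complement is wrongly left out of the outcome.* The list of markers is worded as open.

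Finally, screening began in February 2022, so a draw added later leaves earlier patients without it. That is a real cost of the fix. None of these replies removes the empty week-0 cell or the wrong time point.

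**Conclusion.** The point holds as a limited one about a secondary outcome. IgG and RF have no scheduled value at the start of treatment. Their only pre-dose value is about 4 weeks old and, in patients who entered on that marker, is the selecting value.

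The within-arm artefact is 0.11 to 0.34 SD in patients selected on the marker (cut-off 0.5 SD, r from 0.9 to 0.7). It is about 0.003 to 0.08 SD averaged over the OR rule (cut-off 0 or 1 SD, r from 0.6 to 0.95, inter-marker correlation 0.3). All of these inputs are assumptions. How far a real arm lies towards the larger figures depends on how many patients enter with that marker raised.

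The gap introduces no bias into the randomised contrast, and no effect on the primary endpoint is shown. It deserves attention because the named paired test invites a within-arm reading and the remedy is cheap. The repeated week 12 is a plain error that needs correcting in any case.

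**What to change.** - In Table 2, tick Ig, complement and RF at week 0, on the blood already drawn before first dose.
- Define that value as baseline for the serological outcomes and keep the screening values for eligibility.
- For patients already past week 0, use the screening value as baseline and say so in the report.
- Judge serological change by the between-arm difference adjusted for baseline (for example ANCOVA), not by paired tests within an arm. Methods for additional analyses {20b} currently states that no adjusted analyses are planned, so that sentence must change too.
- In Secondary outcome measure, give the serological time points as 12 and 24 weeks.

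Cost: one extra assay panel per patient (at most 87), no extra visit, and wording changes. The downside is a mixed source of baseline between patients enrolled before and after the change, which should be reported.

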### Sample size {14}

According to the results of our pilot study [24] and clinical experiments, the expected response rate is 70% (μ) in baricitinib + HCQ group, and 30% (μ0) in HCQ group. We use this formula to calculate the sample size:$$N=\frac{{\left({z}_{a/2}+{z}_{\beta }\right)}^{2}{\sigma }^{2}}{{\left(\mu -{\mu }_{0}\right)}^{2}}$$

Zα/2 = 1.96 when alpha = 0.05, Zβ = 0.84 when beta = 0.2. After calculation, the sample will be 46:23. And consider the dropout rate as 20%, we will involve approximately 87 patients (58:29) for the study.

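### The printed sample-size formula does not yield 46:23, and that size has about 90% power (87% by Fisher's exact test) at 70% versus 30%, not the stated 80%

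*Protocol article*

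**What the plan says.** The Sample size section ({14}) gives the planning rates: "the expected response rate is 70% (μ) in baricitinib + HCQ group, and 30% (μ0) in HCQ group". The error rates are "Zα/2 = 1.96 when alpha = 0.05" and "Zβ = 0.84 when beta = 0.2". Introduced by "We use this formula to calculate the sample size", the formula printed is N = (z_α/2 + z_β)² σ² / (μ − μ0)². No value or definition of σ is given. The result is "After calculation, the sample will be 46:23", which a 20% dropout allowance raises to 58:29, or 87 patients.

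Elsewhere, Trial design ({8}) sets the allocation: "Patients will be randomized (2:1) to receive baricitinib 4 mg per day", against HCQ alone. The primary outcome ({12}) is a response rate at week 12, so it is binary. The statistical methods section ({20a}) plans the test: "Categorical variables were analyzed using the chi-square test or Fisher’s exact test, where appropriate", and adds "Two-tailed tests were used for all analyses".

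**The concern.** The formula is the standard one for comparing the mean of one sample with a fixed value. The trial compares two observed proportions in arms of unequal size. A formula with one variance and no allocation ratio cannot by itself lead to a pair of arm sizes such as 46:23, and without σ nobody can repeat the calculation.

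The stated power is also in doubt. If 46:23 is not the 80% answer for the stated inputs, beta = 0.2 does not describe the trial being run. Readers would then be misinformed about how much the design can lose, for example if the true response rate on baricitinib falls below 70%, before power drops under 80%.

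**Working it through.** **Inputs.** p1 = 0.70, p0 = 0.30, difference d = 0.40 and d² = 0.16; z_α/2 = 1.96; z_β = 0.84 (all from Sample size); allocation ratio r = 2 (Trial design); two-sided chi-square or Fisher's exact test (statistical methods section). σ is not given, so the range of plausible readings is shown.

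**1. The printed formula.** (1.96 + 0.84)² = 7.84, so N = 7.84 × σ² / 0.16 = 49 × σ².

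| Reading of σ² | σ² | N |
|---|---|---|
| One binary response at 30% or 70% | 0.21 | 10.3 |
| One binary response, largest possible variance | 0.25 | 12.25 |
| Both arms added, unpooled (0.21 + 0.21) | 0.42 | 20.6 per arm, 1:1 |
| Both arms added, pooled (2 × 0.25) | 0.50 | 24.5 per arm, 1:1 |

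To return 23, 46 or 69, σ² would have to be 0.47, 0.94 or 1.41. None of the readings in the table gives 23 or 46.

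**2. The two-proportion formula.** With control-arm size n, treatment-arm size r·n and p̄ = (p0 + r·p1)/(1 + r):

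n = [z_α/2 √((1 + 1/r) p̄(1 − p̄)) + z_β √(p0(1 − p0) + p1(1 − p1)/r)]² / d²

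For r = 2, p̄ = 0.5667, the first root is 0.6069 and the second is 0.5612.

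- 80% power: (1.96 × 0.6069 + 0.84 × 0.5612)² / 0.16 = 17.24, so 18 controls: 36:18, total 54.
- 80% power with continuity correction: (17.24/4) × [1 + √(1 + 6/(17.24 × 2 × 0.40))]² = 20.8, so 21 controls: 42:21, total 63.
- 90% power (z_β = 1.2816): 22.77, so 23 controls: **46:23, total 69**.

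Two other variants at 80% power are no closer: the unpooled form gives 15.5 controls (32:16) and the arcsine form 17.4 (36:18).

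For r = 1, p̄ = 0.50, the roots are 0.7071 and 0.6481, and 80% power gives 23.29 per arm. Rounding that down to 23 and doubling the other arm also produces 46:23.

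**3. Power at 46:23.** Every possible pair of responder counts was weighted by its binomial probability, and the weights of the pairs with two-sided p < 0.05 were summed.

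| True rates | Uncorrected chi-square | Fisher | Yates |
|---|---|---|---|
| 70% v 30% | 89.9% | 86.7% | 85.7% |
| 65% v 30% | 80.2% | 76.4% | 73.4% |
| 60% v 30% | 66.7% | 63.4% | 57.9% |

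**4. Smallest 2:1 designs with 80% exact power at 70% v 30%.** At 36:18 the figures are 81.1% (chi-square), 79.5% (Fisher) and 73.5% (Yates). Fisher first reaches 80% at 40:20 (80.0%) and Yates at 42:21 (80.4%).

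**5. Dropout.** 46/0.8 = 57.5, rounded up to 58; 23/0.8 = 28.75, rounded up to 29; total 87. This reproduces the plan's figure.

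**The case against.** The best defence is that σ² is undefined. If it means the variance of a difference between two responses, the value needed for 23, namely 0.47, lies between the unpooled 0.42 and the pooled 0.50. A reader might infer that the formula requires an impossible variance; that holds only if σ² is the variance of a single response, which the article does not say. This part of the defence stands. It does not rescue the calculation, because neither value returns 23 and both describe 1:1 allocation.

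A second objection is that 54 is not the only 80% answer. This also stands. A reader might conclude that the trial enrols 19 patients too many (36:18 becomes 45:23, or 68, after dropout). With Fisher the figure is about 40:20, which becomes 50:25, or 75; with Yates it is 42:21, which becomes 53:27, or 80. Since the plan allows chi-square or Fisher, the excess over 87 depends on the test and could be as small as 7.

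Third, a reader might take the 70% rate to be optimistic. The documents do not support that: the Discussion gives the pilot's size (11 patients) and a significant ESSDAI improvement, but no responder rate to set against 70%.

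Finally, the error is harmless in direction, and anyone can recompute power from the rates, alpha and arm sizes given. That limits the consequence, but formula, beta and sample size still contradict one another.

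**Conclusion.** The point holds as an error of justification and reporting. The printed formula does not give 46:23 on any of the readings of σ tried, and beta = 0.2 does not describe that size. At the protocol's own rates and a two-sided 5% level, 46:23 evaluable patients have 89.9% power by uncorrected chi-square, 86.7% by Fisher and 85.7% by Yates. These figures assume independent binomial responses and exactly 46 and 23 evaluable patients.

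Two routes to 46:23 fit: 90% power at 2:1, or a 1:1 calculation at 80% with one arm doubled. The article does not show which was used.

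A reader might infer from a wrong formula that the trial is too small. It is not under its stated assumptions: power exceeds 80% with all three tests, and the dropout inflation is correct. The correction should be made because the stated power is a figure that readers rely on, and the actual margin is test-dependent: 80% power survives a fall to 65% v 30% with the uncorrected chi-square but not with Fisher or Yates.

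**What to change.** In the Sample size section:

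1. Replace the formula with the two-proportion formula for 2:1 allocation, and state whether a continuity correction is used.
2. Say how 46:23 was derived. Keep the 80% planning target visible if that was the target, and give the attained power beside it.
3. Keep 58:29 and add a statement along these lines: *46:23 evaluable patients give about 90% power by uncorrected chi-square (87% by Fisher's exact test) for 70% v 30%; for 65% v 30% power is 80% by chi-square and 76% by Fisher.*

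The cost is a text correction. Enrolment, allocation, endpoint and analysis do not change.

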### Recruitment {15}

Participants will be recruited at eight different centers distributed throughout seven provinces in China. The leadership center, Peking Union Medical College Hospital (PUMCH), is a referral center for difficult and severe rheumatic and autoimmune diseases in China. We believe that enough patients who meet the inclusion and exclusion criteria can be involved in this study.

## Assignment of interventions: allocation

### Sequence generation {16a}

Eligible participants will be randomized into HCQ group or baricitinib + HCQ group with a computer-generated randomization schedule operated at the application of CRDC.

### Concealment mechanism {16b}

Allocation is not concealed and will be revealed to both the patient and the researcher upon randomization.

### Implementation {16c}

Confirmation of eligibility and enrolment of participants into the trial will be assigned to a medical practitioner. After signing the informed consent forms, the researchers will use the computer-generated randomization schedule to allocate the patient to one of the study arms. The study group will be revealed at the same time to both the patient and researcher.

## Assignment of interventions: blinding

### Who will be blinded {17a}

Because this is an open-label study, all the participants and researchers will not be blinded.

### Procedure for unblinding if needed {17b}

The trial design is open label; therefore, there is no unblinding procedure.

## Data collection and management

### Plans for assessment and collection of outcomes {18a}

Data will be collected and saved in the hospital information system (HIS) in each single center. The study will use the CRDC platform and the application of CRDC to follow-up patients. The mobile device application for the CRDC ensures convenient and standardized clinical data collection for this study.

